##### Enhanced implementation strategy bundle

Standard Implementation Strategy Bundle (i.e., Build a Coalition, Implementation Champions, Local Technical Assistance) plusClinician-level Audit and Feedback: Each month, the Implementation Team will e-mail participating LVNs and PCPs a list of their eligible patients who did not receive screening and/or assessment. The report will include a comparison of the percentage of each clinician’s patients who were not screened/assessed relative to other clinicians at that site. Site leadership will continue to receive System-Level Audit and Feedback reports.

#### Period 2 (Crossover Allocation; 3 Months)

At the beginning of Period 2, we will assess Reach and perform crossover allocation. Sites that were initially randomized to standard implementation and are still non-responsive (< 80% Reach) will cross over to enhanced implementation. Sites that were randomized to standard implementation and achieve ≥ 80% Reach will continue to receive standard implementation. Sites randomized to enhanced implementation will receive standard implementation regardless of response.

#### Period 3 (Follow-Up; 3 Months)

All sites will receive standard implementation, and outcomes will be monitored. Calls with champions will focus on developing a Sustainment Plan for each site to hard wire new processes. Champions will consider, “What would be required to make this new process permanent?” Key to supporting Sustainment, during the study, GEC plans to develop an electronic quality measure to report PACT Functional Status Screening Initiative adherence. This will replace the costly and time-intensive External Peer Review Program reporting now in use.

#### Phase 3: Sustainment (6 months)

Implementation support will be withdrawn, and each site will transition to their Sustainment Plan. Implementation and effectiveness outcomes will continue to be evaluated (Tables 2 and 3).

### Outcome measures and sources by aim

#### Aim 1 (Implementation Outcomes)

The primary outcome for Aim 1 is Reach, with secondary outcomes of Adoption, Implementation (fidelity, adaptations), and Maintenance (Table 3). Reach is defined as the proportion of eligible Veterans who receive LVN screening and PCP assessment at each site. We will identify eligible veterans (i.e., ≥ 60 years old, seen in primary care after implementation begins) and use Health Factors to identify completed screening, defined as an LVN completing the electronic tool, and assessment, defined as a PCP reviewing screening results and either (a) documenting via checkbox that further referral is not needed or (b) placing a referral to address impairments.

Adoption is defined as the proportion of LVNs and PCPs at each site who regularly complete screening and assessment. Adequate adoption is defined as ≥ 80% [58]. To identify more nuanced aspects of adoption, we will review a randomly selected subset of charts at each site to examine if clinician notes for the visit when screening was completed have content related to functional status and type of content.

Fidelity to intervention core components will be assessed to determine if core components were implemented as intended, accounting for adaptations and modifications that were consistent vs. inconsistent with intent [48]. Study staff will complete fidelity checklists using electronic health record and qualitative data sources.

Recipient experience will be assessed using periodic reflections for champions, interviews for leadership, veterans, and family caregivers, and surveys for clinicians, and will be used to inform adaptations to intervention components and implementation strategies [59]. To operationalize processes within PRISM’s Adoption, Implementation, and Maintenance domains, we will use Normalization Process Theory (NPT) to guide qualitative data collection [39, 40]. NPT complements PRISM and considers the intervention itself, how staff understand the intervention, attitudes that develop around the intervention, and how it fits into existing roles, systems, and norms. We will use qualitative data to investigate how these processes and constructs shaped implementation and sustainment outcomes.

Maintenance will be measured as continued LVN screening and PCP assessment. We will define adequate maintenance as ≥ 80% at 6 months after beginning Sustainment. To assess clinician capacity for implementation and sustainment, we will use 2 validated survey measures: the short form of the Clinical Sustainability Assessment Tool (CSAT) [60, 61] and Primary Care Team Dynamics (PC-TD) survey [62]. The CSAT short form assesses 7 domains: engaged leadership; engaged clinical partners; organizational readiness; workflow integration; implementation and training; monitoring and evaluation; and outcomes and effectiveness (21 items, Likert scale; higher scores indicate greater capacity for sustainability). The PC-TD subscales measure shared understanding and communication (11 items, Likert scale, higher scores reflect more optimal team dynamics).

To identify potential explanatory factors for outcomes while minimizing burden, we will use existing measures available from administrative data. These include the PACT implementation index score [63], domains of the All Employee Survey (AES; Actions/Behaviors, Climate) [64], and the Federal Employee Viewpoint Survey (FEVS), given to a subset of AES respondents (31 items; domains include employee engagement, burnout) [64]. We will extract pre-post scores for PACT and occupation groups based on available dates most closely aligned with study periods.

#### Aim 2 (Implementation Strategy Effectiveness)

The primary outcome for Aim 2 is Reach, defined as in Aim 1, with ≥ 80% defined as adequate Reach (Table 2). We will assess perspectives on the effectiveness of the standard vs. enhanced implementation strategies using qualitative data.

#### Aim 3 (Clinical Effectiveness)

The primary outcome for Aim 3 is proportion of Veterans with impairments who receive appropriate referrals (Table 3). We will define appropriate referrals as the PCP reviewing the LVN screening results and either (1) documenting via checkbox that further referral is not needed or (2) placing a referral to address identified impairments. We acknowledge that management of functional impairment is complex and there is no “gold standard” for appropriate referrals. For example, a patient may not require a referral because they are already receiving services. Functional status assessment may also inform clinical decision-making (e.g., whether to order cancer screening) but not result in referral. Thus, we will capture clinician judgment of when referrals are appropriate. As noted above, we will use Health Factors data and clinical notes to capture clinician judgement of when referrals are appropriate.

Secondary outcomes include facility-free days, emergency department visits, hospitalization, short- and long-term skilled nursing facility (SNF) use, and functional status. Facility-free days measures the number of days a Veteran is alive and outside a hospital or SNF, calculated from GECDAC residential history files (RHF) [54]. The RHF integrates VA, Medicare (including Medicare Advantage), and Medicaid claims to describe episodes of care for individual Veterans in VA and non-VA settings [65]. We will assess other utilization with GECDAC Core Files [66] and functional status using CDW Health Factors data.

#### Aim 4 (Frailty)

Frailty will be measured using the validated VA Frailty Index (VA-FI), calculated using the cumulative deficit method [67]. The VA-FI includes up to 31 age-related health deficits based on VA EHR diagnostic and procedure codes [46, 68]. Categories include non-frail (0–0.1), pre-frail (0.11–0.2), and frail (> 0.2). Functional status will be measured from Health Factors. In sensitivity analyses, we will examine other EHR frailty indices (e.g., JEN Index [69]).

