### Study goals and objectives

The goals of the PACT Functional Status Screening Initiative are four-fold: (1) measure clinician- and organization-level implementation outcomes; (2) compare the effectiveness of a standard versus enhanced implementation approach to improve adoption; (3) measure patient-level clinical effectiveness of the intervention; and (4) test the effectiveness of electronic health record (EHR)-based frailty screening for identifying veterans at risk for functional impairment.

We will evaluate this initiative by conducting a hybrid type II implementation-effectiveness cluster-randomized adaptive trial [32–34]. During implementation, we will identify sites with low uptake and compare a standard bundle of implementation strategies to an enhanced bundle [35]. Based on our preliminary work [31], we hypothesize that this will lead to increased identification and improved management of functional impairment while providing data to inform VA strategic planning related to long-term services and supports and implementation of new programs. Specifically, we will generate data to guide VA’s investment in non-institutional care programs (including home- and community-based services) that can enhance veterans’ ability age in place. The findings will also allow for targeting and testing of novel programs to address impairments and prevent or delay further functional decline and associated acute care utilization.

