**3. Electronic tools and templates to facilitate LVN screening, PCP assessment, and documentation**
• **Component 3a:** Validated LVN screening tool: (1) brief two-question pre-screener asking about difficulty performing ADLs and IADLs [41], and, among patients who report difficulty on pre-screener, (2) in-depth screener asking about difficulty and needing help with each ADL/IADL [42]. Results used to auto-populate nursing note • **Rationale:** Two-part screener intended to quickly identify patients who would benefit from in-depth screening while “screening out” individuals without impairment, reducing LVN and patient burden. Automation reduces documentation burden
• **Component 3b:** PCP alert and referral menu: If patient screens positive (i.e., reports difficulty/needing help with ≥ 1 ADL/IADL), PCP receives electronic alert linked to referral menu. Alert prompts PCP to review LVN screening results and perform additional assessment as needed. PCP can select up to 5 referrals: physical therapy, occupational therapy, social work, geriatric medicine, prosthetics; referral menus may be adapted at each site to meet local needs and include Community Care referrals • **Rationale:** Addresses clinical partner requests for integration of functional assessment into existing workflows and need for a standardized location to retrieve data on function; alert supports interprofessional approach to measurement; integrated EHR referrals address concerns that data will not be used to inform care and that clinicians lack knowledge of resources, making desired outcome (appropriate referral) more salient for PCPs

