**Fig. 2 Fig2:**
[figure not shown]
Flow Diagram for Adaptive Cluster-Randomized Controlled Trial. The figure shows the sequence of the four implementation periods, randomization, and cross-over allocation

In keeping with our operational partners’ interest in developing proactive approaches to identify high-risk veterans and intervene to prevent or delay functional impairment and associated acute care utilization, we will test the association of clinic-collected functional status measures with automated EHR-based frailty measures. Because frailty typically develops before functional impairment and may be a promising target for intervention [44–47], these findings will clarify how the two approaches might complement and inform one another.

Based on Primary Care and Office of Nursing Services capacity and input, we will implement the intervention in two waves, with 8 sites total. Sites may range in size depending on organizational capacity (e.g., a full community-based clinic or several primary care teams within a larger site). For both waves, we will cluster at the site level. Each site will move through three phases: Pre-Implementation, Implementation, and Sustainment (Fig. 3) [48].

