**Aim 4. Effectiveness of EHR-based frailty screening**								
Association of EHR frailty indices with functional status	VA-FI, JEN FI	X		X	X	X		X

Abbreviations: *CDW* Corporate Data Warehouse, *GECDAC* GEC Data & Analysis Center, *RHF* Residential History File, *VA-FI* VA Frailty Index

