#### Analysis plan, aim 4 (Frailty)

Our primary exposure for Aim 4 is ‘frailty’ operationalized using the VA-FI. We will model the VA-FI as a 3-level categorical measure (i.e., non-frail, pre-frail, frail). Using a similar modeling strategy as for Aims 1–3, we will use an ordinal logistic mixed modeling strategy to estimate the association of clinic-collected functional status measures on frailty (VA-FI; sensitivity analyses with other measures [69]). Inference will be based on estimated odds ratios associated with functional status measures, with associated 95% CIs and/or *p*-values.

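### Aim 4 does not fix which frailty index value is related to the functional screen, so codes arising after a positive screen can enter the index and inflate the association

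*Protocol article*

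**What the plan says.** - **Purpose.** Study goals and objectives gives the fourth goal as to "test the effectiveness of electronic health record (EHR)-based frailty screening for identifying veterans at risk for functional impairment". Overview of study design gives the reasoning: "Because frailty typically develops before functional impairment and may be a promising target for intervention".
- **Index.** Under Aim 4 (Frailty), "The VA-FI includes up to 31 age-related health deficits based on VA EHR diagnostic and procedure codes". The three categories have cut-offs at 0.1 and 0.2. The deficits are not listed in the article.
- **Function.** The same section states: "Functional status will be measured from Health Factors". These are the data generated by the clinical screening tools.
- **Schedule.** The Table 3 row "Association of EHR frailty indices with functional status" is marked at pre-implementation, P1, P2, P3 and 6 M. It is blank at the run-in and at 3 M.
- **Model.** Analysis plan, aim 4 names frailty as the primary exposure and then says "we will use an ordinal logistic mixed modeling strategy to estimate the association of clinic-collected functional status measures on frailty". Frailty category is therefore the dependent variable and function the predictor.
- **What a positive screen sets off.** Under Table 1, component 3b, the primary care provider receives an alert to review the result and assess further as needed, and "PCP can select up to 5 referrals: physical therapy, occupational therapy, social work, geriatric medicine, prosthetics".

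**The concern.** An index meant to flag veterans at risk should be fixed before the state it flags is measured. The stated schedule and model do not secure that order. Four of the five scheduled time points fall after screening has begun in the run-in. From then on, only screen-positive veterans trigger the alert and its referral menu. If the resulting contacts record diagnoses or procedures that count as deficits, the index rises because the screen was positive, and the association then partly measures the initiative's own activity.

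At stake is the reading of Aim 4: whether an automated index can complement clinic screening. An association partly created by the screen would make the index look more informative than it would be in a clinic that had not yet screened anyone.

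**Working it through.** The article gives no sample size, power or effect size for Aim 4, so there is no figure of its own to reproduce. Three checks were made.

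**1. Order of events.** Screening starts in the 3-month run-in and is annual. Implementation lasts 12 months and sustainment 6, so the last scheduled association falls at about 12 + 6 = 18 months after launch. A veteran screened in the run-in need not be screened again for about a year, so that veteran's index values in Periods 1 to 3 would generally follow the screen. The pre-implementation value precedes it, but no section pairs that value with the later screen. The initiative's own screen does not exist at pre-implementation. Baseline measures come from data already available (section on developing measures and data), and the earlier screening described in the Background covered ages 75 and older with low uptake, whereas the initiative covers ages 60 and older.

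**2. Step size of the index.** With all 31 items, the index is k/31 for k deficits.
- One deficit: 1/31 = 0.032.
- 3/31 = 0.097 (non-frail) and 4/31 = 0.129 (pre-frail).
- 6/31 = 0.194 (pre-frail) and 7/31 = 0.226 (frail).

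One added deficit changes the category only for veterans with exactly 3 or 6 deficits.

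**3. Illustrative size.** Inputs:
- From the article: impairment prevalence 459,000 / 2,800,000 = 16.4% (ages 65 and older, Background), 31 deficits, and the cut-offs.
- Assumed: no true association; a negative binomial deficit count with size 4 and mean 3 to 6; and a share q of screen-positive veterans who gain exactly one counted deficit.

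If p(k) is the distribution among screen-negatives, that among screen-positives is s(k) = (1 − q)·p(k) + q·p(k − 1). A proportional-odds model, logit P(category ≤ j) = a_j − b·x with x = 1 for a positive screen, is fitted to the two sets of category probabilities. The spurious odds ratio is exp(b).

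| q | mean 3 | mean 4 | mean 5 | mean 6 |
|---|---|---|---|---|
| 0 | 1.00 | 1.00 | 1.00 | 1.00 |
| 10% | 1.076 | 1.063 | 1.054 | 1.048 |
| 25% | 1.197 | 1.163 | 1.141 | 1.126 |
| 50% | 1.420 | 1.348 | 1.301 | 1.267 |
| 100% | 1.959 | 1.798 | 1.685 | 1.608 |

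The share of veterans with exactly 3 or 6 deficits is 22.3%, 23.8%, 23.0% and 21.1% for means 3, 4, 5 and 6.

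Hand check for mean 3, q = 50%. Here p(3) = 20·(4/7)^4·(3/7)^3 = 0.168, and 0.653 of veterans are non-frail.
- Non-frail among screen-positives: 0.653 − 0.5 × 0.168 = 0.569.
- Odds of being at least pre-frail: 0.431/0.569 = 0.757, against 0.347/0.653 = 0.531 in screen-negatives.
- Ratio: about 1.43 at the lower cut-off, in line with the fitted 1.42 over both cut-offs.

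Restricting the index to codes dated before the screen sets q = 0, and the spurious odds ratio is 1.00.

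**The case against.** The strongest reply has four parts.

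- **A pre-launch measurement is planned.** This is true: Table 3 marks pre-implementation. A reader might infer that the index is measured only after launch, and the table does not support that. But no section makes the pre-implementation index the primary value or links it to the initiative's screen.
- **The look-back window belongs in the full protocol or analysis plan.** Its length does, and its absence from an article is no fault. Nor does a mark under P1 prove that post-screen codes will be counted. The point rests on what the article does state: an early-warning purpose, a schedule mostly after launch, and a model with frailty as the outcome. These do not fit together.
- **The mechanism is not demonstrated.** This stands. A reader might infer that the association is biased upwards and grows with follow-up. The documents do not show it: the 31 deficits are not listed, assessment is as needed, referral is optional, and the Aim 3 outcome section notes that a veteran may already be receiving services. Screen-negative veterans can also acquire codes in usual care. Inflation is possible, not established.
- **A concurrent association is a fair question.** Overview of study design also asks how the two approaches might inform one another, and concurrent values can serve that. They do not answer the fourth goal as worded.

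**Conclusion.** The point holds as a gap in the stated design. The article does not fix which frailty index value is related to the initiative's screen, and its schedule and model let codes recorded after a positive screen enter an index meant to precede impairment. Any artefact from screen-prompted coding would push the association upwards.

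Its size cannot be derived from the documents. Under the assumptions above it is small if few positive screens add a counted deficit (odds ratio 1.05–1.08 at 10%) and becomes material if many do (1.13–1.20 at 25%, 1.27–1.42 at 50%). Both the share and the deficit distribution are assumptions. The model direction does not create the bias by itself, but it contradicts the label of exposure and leaves the time order open.

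The point concerns the fourth of four goals and does not touch the primary implementation or clinical effectiveness outcome. It is worth correcting because the correction is cheap and removes this artefact by construction.

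**What to change.** Add to the Aim 4 analysis plan that, for the primary association, the VA-FI is calculated from codes dated before each veteran's first initiative screen and is related to the result of that screen. Apply the same rule to the JEN index in the sensitivity analysis. The pre-implementation value would also serve, although it would be up to 12 months old for a veteran first screened at the end of the implementation phase. Reword the model sentence so that the role of frailty agrees with its description as the exposure. Keep the concurrent associations in Periods 1 to 3 and at 6 months as secondary or sensitivity analyses.

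The cost is a date filter on record data that the plan already uses, and a sentence or two of text. The small loss is that the repeated post-launch values no longer support the primary inference.

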### Analysis

#### Analysis Plan, Aim 1 (Implementation Outcomes)

We will use descriptive statistics to examine patient- and site-level baseline measures, including outcome measures. For the primary outcome of Reach (0–100%), we will fit three-level mixed effects linear regression models that properly account for the longitudinal design and clustering of patients within sites. Our primary interest is whether baseline characteristics are associated with increased Reach. Inference will be determined using odds ratios and 95% confidence intervals (CIs) and/or *p*-values. A similar strategy will be employed for each secondary outcome.

To analyze Aim 1 qualitative data, we will use rapid analysis methods developed for implementation research that will allow us to use these data in real time to inform implementation strategies [70, 71]. The evaluation team will first develop summary templates with sections corresponding to each PRISM domain and NPT construct. Following each data collection instance, we will summarize key points in the appropriate section of the template; illustrative quotations will be included in summaries. A second team member will review the primary data source and summary for accuracy. We will use matrix analysis to synthesize template data, a method of displaying data to identify relationships between and across units of analysis [70]. Matrices will be organized by site to compare outcomes across sites and type of pre-implementation approach to measurement. Team members will meet regularly to discuss results.

#### Analysis plan, aim 2 (Implementation Strategy Effectiveness)

The primary outcome for Aim 2 is the proportion of sites that achieve ≥ 80% Reach. As in Aim 1, we will first describe site characteristics by implementation strategy bundle (standard vs. enhanced) and baseline proportions of screening and assessment. We will also fit mixed effects logistic regression models where the unit of analysis is the site, accounting for the longitudinal (repeated measures) design and for covariates such as level of champion engagement. Our primary interest is effectiveness of the standard vs. enhanced approach. Inference will be determined using odds ratios and 95% CIs and/or p-values. A similar strategy will be employed for secondary outcomes. We will compare recipient perspectives on the standard vs. enhanced approach using methods as in Aim 1 and triangulate qualitative and quantitative data on effectiveness of strategy bundles [65].

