#### Period 1 (Randomization to Standard or Enhanced Implementation; 3 months)

Our adaptive trial design will deploy resources to sites with the greatest need for enhanced implementation strategies [32–34]. After the Run-In period, data generated by the clinical screening tools (“Health Factors” data) will be used to identify sites with inadequate Reach, defined as < 80% of eligible veterans receiving LVN screening and/or PCP assessment (in keeping with standard benchmarks for adequate adherence to practice guidelines) [58]. We will define PCP assessment as reviewing LVN screening results and either (1) documenting via checkbox that further referral is not needed or (2) placing a referral to address identified impairments. We chose both LVN screening and PCP assessment as the benchmark for implementation response because these combined steps contribute to improved identification (via screening) and management (via assessment/referrals). Sites with ≥ 80% Reach at the end of the Run-In phase will receive the standard implementation bundle for all phases of implementation. For sites with < 80% Reach, we will randomize 1:1 by site to 3 additional months of standard vs. enhanced implementation. Based on current levels of functional status measurement in VA primary care practices (51% measuring function among ≥ 80% of eligible veterans), we anticipate that half of included sites (*n* = 4) will require enhanced implementation. The enhanced implementation strategy bundle will include the components of the standard bundle above (i.e., Coalition Building, Implementation Champions, Technical Assistance) plus clinician-level audit and feedback for participating LVNs and PCPs instead of site-level audit and feedback.

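### Aim 2 rests its inference on a site-level mixed logistic model of a binary outcome with about four randomised sites, which cannot give a dependable odds ratio or p-value

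*Protocol article*

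**What the plan says.** All references are to the protocol article.

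- **Size.** Under the description of Fig. 2: "we will implement the intervention in two waves, with 8 sites total".
- **Who is randomised.** Under Period 1, sites below 80% Reach after the run-in are randomised: "we will randomize 1:1 by site to 3 additional months of standard vs. enhanced implementation". Sites at or above 80% stay on standard implementation and are not randomised.
- **How many.** The same section gives "we anticipate that half of included sites (*n* = 4) will require enhanced implementation", based on a current-practice rate of "51% measuring function among ≥ 80% of eligible veterans".
- **Outcome.** The Aim 2 analysis plan states: "The primary outcome for Aim 2 is the proportion of sites that achieve ≥ 80% Reach". Table 2 lists the same measure for standard versus enhanced.
- **Model.** The Aim 2 analysis plan continues: "We will also fit mixed effects logistic regression models where the unit of analysis is the site". It adds the repeated-measures structure and covariates, with champion engagement as the example. Inference is to come from odds ratios with 95% confidence intervals and/or p-values.
- **Crossover.** Under Period 2, standard-arm sites still below 80% move to enhanced implementation. All enhanced-arm sites move to standard, whatever their response.
- **Power.** The power statement covers only the Aim 3 referral outcome.

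**The concern.** Four sites split two and two, each scored yes or no, carry almost no information for a logistic model. Such data are usually separated, meaning that one arm is all successes or all failures, and the odds ratio is then infinite, zero or undefined. A random-site variance and covariate effects would have to be estimated from the same four sites.

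Aim 2 is the comparison for which the adaptive randomisation was designed, and the Discussion says that its result will inform system-wide implementation. If the plan is followed literally, the main result may be non-estimable. It may also be a software p-value that looks significant without a valid basis.

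**Working it through.** **Step 1. Reproduce the plan's figure.** With 51% of practices meeting the benchmark, 8 × (1 − 0.51) = 3.92, which rounds to the stated 4. At 1:1 this is 2 versus 2.

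**Step 2. Which period carries the randomised contrast.** At the run-in, every randomised site is below 80% by definition, so baseline status adds no binary information. From Period 2 the arms no longer keep their assigned strategies. The concurrent randomised contrast is therefore Period 1, with one binary result per site.

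**Step 3. Estimability in Period 1.** Each arm can have 0, 1 or 2 successes out of 2, so there are 3 × 3 = 9 tables. The odds ratio is finite only if both arms have exactly one success: (1 × 1)/(1 × 1) = 1. The other eight tables are separated or undefined. With assumed true success rates of 20% and 80%, the chance of a finite odds ratio is (2 × 0.2 × 0.8) × (2 × 0.8 × 0.2) = 0.32 × 0.32 = 0.10.

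**Step 4. Smallest attainable exact p.** There are C(4,2) = 6 possible allocations. The most extreme result, 0/2 versus 2/2, has two-sided p = 2/6 = 0.333. Fisher's exact test for other numbers of randomised sites gives:

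| Randomised sites | Split | Smallest two-sided p |
|---|---|---|
| 3 | 1 v 2 | 1/3 = 0.333 |
| 4 | 2 v 2 | 2/6 = 0.333 |
| 5 | 2 v 3 | 1/10 = 0.10 |
| 6 | 3 v 3 | 2/20 = 0.10 |
| 7 | 3 v 4 | 1/35 = 0.029 |
| 8 | 4 v 4 | 2/70 = 0.029 |

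At seven or eight sites, p < 0.05 needs a perfect split between arms. At 4 versus 4 with assumed rates of 20% and 80%, power is the chance of a perfect split in either direction: 0.8⁸ + 0.2⁸ = 0.168.

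**Step 5. Do repeated periods rescue the model?** A random-intercept logistic model was simulated with no treatment effect: four sites, three periods, an average success probability of one half on the logit scale, arm labels held fixed and no covariates. Between-site SDs on the logit scale are assumptions. The test was a likelihood-ratio test at nominal 5%. An estimate was called divergent if the log odds ratio exceeded 8, or the intercept 12, in absolute value.

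| Assumed site SD | Rejections at nominal 5% | Divergent estimates |
|---|---|---|
| 1 | 10% | 14% |
| 2 | 16% | 30% |
| 4 | 19% | 52% |

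**Step 6. What Reach as a proportion offers.** A two-sample t interval on site-level Reach with 2 versus 2 has 4 − 2 = 2 degrees of freedom and critical t = 4.30. Its half-width is 4.30 × s × √(1/2 + 1/2) = 4.30 s, where s is the between-site SD. Power under normality is 0.22 for a difference of 2 SDs and 0.57 for 4 SDs. Adding one covariate leaves 4 − 3 = 1 degree of freedom and critical t = 12.7. With s unchanged, power falls to about 0.13 and 0.25.

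**The case against.** The best defence is that the planned model is longitudinal, that the analysis starts with description and is triangulated with qualitative data, that no power is claimed for Aim 2, and that small-sample or penalised methods are commonly left to an SAP. Part of this stands: a repeated-measures model does not always fail, and the article is not at fault for leaving out such detail. However, the outcome, unit, model and basis for inference are all fixed in the text. Step 5 shows that extra periods do not make the p-value trustworthy.

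Stronger readings that a reader might infer are not supported:

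- *The outcome section contradicts the analysis section.* The outcome section says "The primary outcome for Aim 2 is Reach, defined as in Aim 1", which alone suggests Reach as a proportion. The sentence then gives the 80% threshold and refers to Table 2, which agrees with the analysis plan. The wording is loose, not contradictory.
- *Aim 2 is the only randomised question.* The Aim 3 analysis plan also compares standard with enhanced.
- *Significance is impossible in about 97% of realisations.* This follows if the number of low-uptake sites is binomial with 8 sites and rate 0.49, since seven or more then has probability 0.031. It treats a current-practice rate as an independent failure rate after the run-in, and it applies Fisher's test, which the protocol does not plan. The Discussion also allows for Reach lower or higher than expected.
- *Significance can never be reached.* An exact p of 0.029 is possible with seven or eight sites, and software may print p < 0.05 with fewer.

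It is also fair to say that dichotomising is not the main limit. The number of sites is, and Step 6 shows that Reach as a proportion remains imprecise.

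**Conclusion.** The concern holds for the number of sites that the protocol itself expects. With 2 versus 2, eight of nine Period 1 tables give no finite odds ratio and the exact two-sided p cannot fall below 0.333; with five or six sites the floor is 0.10. These results need no assumption beyond 1:1 allocation by site. The false-positive rates of 10–19% and divergence of 14–52% rest on the assumed site SDs of 1 to 4 and on a simplified model without covariates or crossover. They show that inference from this kind of model is unreliable, not that every fit fails. Sites at or above 80% after the run-in may be included in the model, but they are not randomised and add no randomised evidence.

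**What to change.** In the Aim 2 analysis plan and Table 2, with the Aim 2 outcome section worded to match:

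1. Make the primary measure Period 1 Reach, as a proportion at each randomised site.
2. Report the run-in and Period 1 values of every randomised site.
3. Estimate the enhanced-minus-standard difference in site-level Reach, or in change from run-in (choose one in advance). Give a t-based interval on the available degrees of freedom (2 with four sites) and no further covariates.
4. Keep the number of sites at or above 80% as a descriptive count.
5. Drop the site-level logistic odds ratio and p-value, and present Aim 2 as estimation, not a significance test.
6. Describe the non-randomised sites separately.

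This changes wording only and uses data already to be collected. Aim 2 gives up a significance claim, and its interval will be wide because the number of sites does not change.
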